### Measures

2.5

#### Feasibility and acceptability

2.5.1

Overall recruitment, retention, and adherence rates will be calculated as a part of the feasibility assessment. Satisfaction with the VR program will be measured using three items on a 5-point Likert scale (1 = extremely disagree, 5 = extremely agree) modified from the items used in Xu team’s VR exergame study (37). Usability of the VR program will be assessed using four items of the Usability scale from the Augmented Reality Immersion (ARI) Questionnaire rated on a 7-point Likert scale (1 = totally disagree, 7 = totally agree) (38). In each item, the phrase ‘AR application’ will be replaced with ‘VR program.’ Safety of the VR program will be assessed using the VR Sickness Questionnaire (VRSQ; 39), modified from the Simulator Sickness Questionnaire (40). The VRSQ consists of nine items on two components: oculomotor (four items); and disorientation (five items). Each item is rated on a 4-point scale (0 = none, 3 = severe). One open-ended question item is included asking if participants experienced any discomforts or side effects other than those specified in the VRSQ.

#### Perceived restorativeness (phase I only)

2.5.2

Perceived restorativeness is measured using a modified version of the Perceived Restorativeness Scale (PRS) that reflects four key dimensions of the ART (41, 42). The measure consists of six items with three dimensions: being away, fascination, and coherence. Each item is rated on a 7-point Likert scale (1 = not at all, 7 = completely). Perceived restorativeness can be assessed by averaging the values of all six items. Tabrizian et al.’s immersive VR study using the same PRS measure reported Cronbach’s α of the measure as 0.76 (42).

#### Perceived stress

2.5.3

Perceived stress will be measured using a 10-item modified version of the Perceived Stress Scale (PSS; 43). The measure evaluates the degree to which a participant has perceived life as unpredictable, uncontrollable, and overloading over the past week. Each item is rated on a 5-point Likert scale (0 = never, 4 = very often). Total PSS score is obtained by summing all items, where higher scores indicate higher levels of perceived stress. Gillani et al.’s study utilizing the same PSS measure for perceived stress over the past week for diabetic adults reported Cronbach’s α of 0.81 (44).

#### PROMIS^®^ measures

2.5.4

The Patient Reported Outcome Measurement System (PROMIS^®^) is a system of highly reliable and precise measures of patient-reported health on physical, mental, and social well-being (45). Total sum scores are converted to T-scores, which are standardized scores with a mean of 50 and a standard deviation (SD) of 10. Higher scores represent more of the concept that is being measured. These measures will be delivered using Computer Adaptive Testing (CAT), if available. If CAT is not available, participants will complete the questionnaires using the short/fixed forms (4-10 items, each). The following PROMIS^®^ measures will be employed in this research:

Fatigue: PROMIS^®^ Item Bank v1.0 - FatigueSleep disturbance: PROMIS^®^ Item Bank v1.0 - Sleep DisturbanceDepression: PROMIS^®^ Item Bank v1.0 - Emotional Distress - DepressionAnxiety: PROMIS^®^ Item Bank v1.0 - Emotional Distress - AnxietyCognition: PROMIS^®^ Item Bank v2.0 - Cognitive FunctionGlobal health: PROMIS^®^ Scale v1.2 - Global Health

#### NIH toolbox measures

2.5.5

The NIH Toolbox measures are a series of well-validated and reliable measures of patient self-reported health outcomes that assess cognitive, emotional, sensory, and motor functions (46). In this research, the NIH Toolbox Item Bank v3.0 - Loneliness (Ages 18+) - Fixed Form and the NIH Toolbox Item Bank/Fixed Form v2.0 - Self-Efficacy (Ages 18+) will be used to assess loneliness and self-efficacy. The loneliness measure is rated on a 5-point Likert scale ranging from 1 to 5, and the self-efficacy measure is rated on a 4-point Likert scale ranging from 1 to 4, with higher scores indicative of higher levels of the concept being measured. The self-efficacy measure will be delivered using CAT, and the loneliness measure will be assessed using the 5-item fixed form.

#### Caregiver burden

2.5.6

Caregiver Burden will be measured using the Caregiver Reaction Assessment (CRA; 47). The CRA is a 24-item self-administered scale that measures the positive and negative effects of caregiving in five domains: caregiver esteem (7 items), impact on finances (3 items), impact on health (4 items), impact on schedule (5 items), and lack of family support (5 items). The items are rated on a 5-point Likert scale (1 = strongly disagree, 5 = strongly agree), and mean scores are calculated for each domain. Higher mean scores indicate greater caregiver burden with the exception of caregiver esteem. Mean scores range from 1 to 5. The measure is a valid and reliable for use in caregivers of cancer patients (48).

#### Health-promoting behaviors

2.5.7

Health-promoting behaviors will be measured using the Health-Promoting Lifestyle Profile II (HPLP-II; 49). The HPLP-II is a is a self-administered 52-item instrument that measures the frequency of self-reported health behaviors. It consists of six subscales: health responsibility, interpersonal relations, nutrition, physical activity, spiritual growth, and stress management. It is a 4-point Likert type scale (1 = never, 4 = routinely) with possible scores ranging from 52 to 208. Higher scores indicate the more frequent engagement in health behaviors. The HPLP-II and its subscales have been performed reliably well in other studies of caregivers (50).

#### Mutuality

2.5.8

Mutuality will be measured using the Family Caregiver Inventory (FCI) Mutuality Scale (51). The FCI scale is a 15-item questionnaire that addresses the relationship dimensions of reciprocity, love, shared pleasurable activities, and shared values between the caregiver and the care recipient. Each item is rated on a 5-point Likert scale (0 = not at all, 4 = a great deal). The average of all items across the four overarching themes produces a total mutuality score. The scale has demonstrated high levels of reliability, with Cronbach’s α ranging from 0.91 to 0.95 (51, 52).

#### Biomarkers from saliva samples

2.5.9

Saliva samples will be collected by the passive drool method using an open tube and straw or saliva collection aid in a tube. Participants will allow the pooled drool to fall into a straw or a saliva collection aid that leads into a tube and will be asked to fill the tube with approximately 2mL of saliva. The following stress biomarkers will be analyzed from saliva samples: Cortisol, α-amylase, Osteocalcin, Oxytocin.

#### Biomarkers from blood samples (phase II only)

2.5.10

Approximately 4 tablespoons of venous blood will be collected for cardiovascular, metabolic and inflammatory biomarkers. The following assays will be performed: nuclear magnetic resonance lipid analysis, multiplex cytokine immunoassay.

### Data analysis and sample size estimation

2.6

For Phase I, a sample size of 12 is considered since this number is recommended to justify the study feasibility and precision of the mean and variance (53). To account for a 20% attrition rate, Phase I study will enroll up to 15 caregivers. To estimate a sample size for Phase II study, power analysis was performed based on the primary outcome. We used a two-sided hypothesis that the stress level will differ between Active VR group and Sham VR group. In order to detect a difference between Active VR group and Sham VR group, we will need 39 caregiver participants in each group and a total sample size of 78 based on an effect size of 0.6 and correlation of 0.80 between two time points from our previous stress reduction study (54), with 80% power and type 1 error of 0.05. To account for a 20% attrition rate, this study will enroll up to 94 caregivers.

In Phase I, feasibility, acceptability, and perceived restorativeness will be evaluated using descriptive statistics appropriate to the levels of measurement. Friedman test or linear mixed models will be used to test changes in stress measured weekly from Time 0 to Time 4. In Phase II, linear mixed repeated measures analysis will be used to analyze the effects of Active VR on stress compared to Sham VR. Any demographic covariates will be included in the model if significantly associated with the outcomes and significantly different between the two groups. All qualitative data, including written comments on open-ended questions and transcriptions of audio from the phone call follow-up and exit-interview, will be subjected to coding and qualitative data analysis.

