### Participants

2.2

The research protocol will include adults (18 years and older) who serve as a primary caregiver for an adult (18 years and older) planning to undergo an allogeneic HSCT at the NIH Clinical Center. If more than one caregiver is planned for the transplant recipient during the transplant phase, only one primary caregiver will be eligible to participate in this study. Phase I will enroll up to 15 caregiver participants, and Phase II will enroll up to 94 caregiver participants (please see “2.6 Data analysis and sample size estimation” section). Inclusion/exclusion criteria are as follows:

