#### Randomization

2.4.1

In Phase II, all caregiver participants will be randomized into either Active VR group or Sham VR group using permuted block randomization with an allocation ratio of 1:1. All investigators will remain blind to the randomization scheme until each study participant is deemed eligible and signs the consent form. Once each participant is randomly assigned, the participant and the research team members will be aware of the group assignment status.

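### Enrolling 94 does not cover 20% attrition from the 78 participants that Phase II needs: 94 leaves about 75 completers and covers about 17%

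*Protocol article*

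**What the plan says.** Section 2.6 (Data analysis and sample size estimation) derives the Phase II size from a two-sided comparison of stress between the arms. It states that "we will need 39 caregiver participants in each group and a total sample size of 78". The inputs named there are a standardised effect of 0.6, a correlation of 0.80 taken from an earlier study, a power of 80% and a 5% significance level. The allowance for loss follows: "To account for a 20% attrition rate, this study will enroll up to 94 caregivers". Section 2.2 (Participants) gives the same ceiling: "Phase II will enroll up to 94 caregiver participants". Section 2.4.1 (Randomization) specifies "permuted block randomization with an allocation ratio of 1:1", so 94 means 47 per arm.

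The article does not define attrition in any special way and offers no other source for 94. The planned Phase II analysis is a linear mixed model for repeated measures. Section 2.4 schedules a survey at each of five time points, from Day 0 to Day 28.

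**The concern.** An attrition rate is a share of the people enrolled. To end with n completers after losing a fraction d, a trial must enrol n / (1 − d). Adding d × n to the requirement, which is n × (1 + d), gives too few, because the loss applies to the larger enrolled number as well as to n. The stated 94 looks like the second calculation.

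At stake is whether the enrolment figure delivers the sample on which the stated 80% power rests. The figure appears in two sections, so recruitment and later reporting would both inherit it.

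**Working it through.** **Inputs**, all from section 2.6 except the allocation ratio (section 2.4.1): required total n = 78 (39 per group), attrition d = 0.20, stated enrolment 94, effect size 0.6, correlation 0.80, two-sided α = 0.05, power 80%, allocation 1:1.

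**1. Reproducing the stated figure.**
- n × (1 + d) = 78 × 1.2 = 93.6, rounded up to 94. Per group, 39 × 1.2 = 46.8, rounded up to 47, and 2 × 47 = 94.
- n / (1 − d) = 78 / 0.8 = 97.5, rounded up to 98 (49 per group). This does not give 94.

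**2. What 94 delivers.**
- Completers at 20% attrition: 94 × 0.8 = 75.2, or 37.6 per group. The shortfall against 78 is 78 − 75.2 = 2.8, about 3.
- Attrition at which 94 still leaves 78: 1 − 78/94 = 17.0%.
- Check of 98: 98 × 0.8 = 78.4, which is at least 78.

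**3. Phase I as a cross-check.** Phase I goes from 12 to 15 with the same 20% rate. Division gives 12 / 0.8 = 15. Multiplication gives 12 × 1.2 = 14.4, which also rounds up to 15. Phase I fits both rules and does not show which one was used.

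**4. Effect on power.** The article does not state its power formula, so this step rests on an assumed variance model. Let f be the variance of the analysed score relative to a single measurement, with correlation ρ = 0.80:
- mean of k visits: f = (1 + (k − 1)ρ) / k, which is 0.90 for k = 2 and 0.85 for k = 4;
- change score: f = 2(1 − ρ) = 0.40;
- baseline-adjusted score: f = 1 − ρ² = 0.36.

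Power comes from the noncentral t distribution with noncentrality 0.6 / √(2f / n per group) and 2 × (n per group) − 2 degrees of freedom. It is compared at 39 per group (78 in total) and 37.5 per group (75 in total).

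| Assumed model | f | Power at 78 | Power at 75 | Loss (points) |
|---|---|---|---|---|
| Mean of 4 visits | 0.85 | 81.0% | 79.4% | 1.6 |
| Mean of 2 visits | 0.90 | 78.7% | 77.1% | 1.6 |
| Change score | 0.40 | 98.5% | 98.2% | 0.3 |
| Baseline-adjusted | 0.36 | 99.2% | 99.0% | 0.2 |

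The averaging models come closest to the stated 39 per group. With 4 visits, 38 per group gives 79.95% and 39 gives 81.0%, so 39 is the smallest size above 80%. With 2 visits, the normal approximation gives 39.2 per group. The change-score and baseline-adjusted models would need only 18 and 16 per group by the normal approximation, so they do not explain 39. They are shown because the article does not rule them out, and they mark the lower end of the possible loss.

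**The case against.** The strongest reply is that the discrepancy has little consequence. The linear mixed model can use the early visits of a participant who later leaves, so the number contributing data lies somewhere between 75 and 94, depending on when people leave. The 20% is itself a planning figure for which the article gives no source, and if attrition is 17% or less, 94 delivers 78.

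Most of this stands, and it limits the size of the point. It does not make the figures agree. The article sets 78 as the requirement, chooses to inflate it for attrition, and does not use partial follow-up data to justify 94.

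A reader might go further than the article allows in four ways:
- **That only about 75 will be analysed.** The 75 are completers; the mixed model may include others.
- **That Phase I shows the authors dividing there and multiplying here.** It does not, because both rules give 15.
- **That the shortfall cannot be made good.** The 94 is a ceiling, but a ceiling can be amended.
- **That the trial is shown to be underpowered.** The loss depends on a formula the article does not give, and it ranges from negligible to about 1.6 points.

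**Conclusion.** The enrolment figure is wrong as stated. The required 78, the 20% attrition and the cap of 94 cannot all hold together. This part rests only on the article's own numbers and on the ordinary meaning of an attrition rate as a proportion of those enrolled.

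The consequence is small: about 3 completers, equivalent to 4 enrolments (98 − 94). Any statement about lost power is conditional on the assumed variance model. The point is an arithmetic correction that is worth making because it is cheap and because the figure is stated in two places. It does not call the design or the analysis into question.

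**What to change.** Make the attrition rate, the enrolment cap and the number of completers agree in sections 2.2 and 2.6. Any one of these does it:
- Keep 94 and state that it allows for about 17% attrition.
- Keep 94 and 20%, state that about 75 completers are expected, and give the power for that number under the sponsor's own formula.
- If 78 completers at 20% attrition are preferred, set the cap at 98 (49 per group) in both sections.

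The first two cost a sentence or two and a slightly less favourable stated attrition or power. The third costs 4 more enrolments. If the sponsor expects the mixed model to recover information from participants who leave early and wishes to rely on that, section 2.6 should say so.

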### Design

2.1

The proposed study is a single site, two-phase study targeting allogeneic HSCT caregivers. The Phase I of the study is a single-arm pre-post design to assess the feasibility and acceptability of the nature-based immersive VR program in HSCT caregivers. The Phase II of the study is a prospective randomized controlled trial (RCT) design to examine the effectiveness of the nature-based immersive VR program on stress and symptoms compared to a nature-based non-immersive VR program in the target population. This study followed the Consolidated Standards of Reporting Trials (CONSORT) reporting guidelines for RCTs (**Supplementary Table S1**). In Phase I, all caregiver participants will be given the nature-based immersive VR program. We hypothesize that the majority of caregiver participants will perceive the nature-based immersive VR program as usable, safe, and restorative and show improved levels of stress and symptoms at Time 4 (Day 28) compared to Time 0 (Day 0). In Phase II, caregiver participants will be randomly assigned to one of two groups: nature-based immersive VR program (Active VR) and nature-based non-immersive VR program (Sham VR). We hypothesize that caregiver participants assigned to Active VR will show improved levels of stress and symptoms at Time 4 compared to those assigned to Sham VR. If we identify any weaknesses or gaps in the results of Phase I, such as dissatisfaction with the program (e.g., content, length of the video, difficulty in use) and discomfort with the headset, we plan to make appropriate adjustments prior to initiating Phase II.

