At each time point, all participants will be asked to complete a survey that will be delivered via the Research Electronic Data Capture (REDCap) system.^3^ The surveys at Time 0 (Day 0) and Time 4 (Day 28) will take about 20 to 30 minutes, and the surveys at Time 1 (Day 7), Time 2 (Day 14), and Time 3 (Day 21) will take about 3 to 5 minutes. The participants will be invited to a phone call follow-up at Time 1 and an exit interview at Time 4. Clinical assessments will be performed at Time 0 baseline visit and at Time 4 visit. Saliva samples will be collected three times at Time 0 baseline visit (pre-initial VR program, immediately post-initial VR program, 20 minutes post-initial VR program) and at Time 4 visit (pre-VR program, immediately post-VR program, 20 minutes post-VR program). To index cortisol awakening response, the participants will be instructed to collect three saliva samples (immediately post-awakening, 30 minutes post-awakening, nighttime) within three days of Time 0 and Time 4. In Phase II, blood samples will be collected at Time 0 baseline visit and at Time 4 visit. The schedule of activities or schema of Phase I and II are presented in **Figures 3**, **4**.

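### Phase I hypothesises improved stress at Day 28 compared with Day 0, but the Friedman option is an omnibus five-week test that can be significant when the two days do not differ; the Time 4 minus Time 0 contrast should be named (minor)

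*Protocol article*

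**What the plan says.** Section 2.1 (Design) describes Phase I as a "single-arm pre-post design to assess the feasibility and acceptability of the nature-based immersive VR program in HSCT caregivers". Its hypothesis has a perception part (usable, safe, restorative) and an outcome part: participants will "show improved levels of stress and symptoms at Time 4 (Day 28) compared to Time 0 (Day 0". The outcome part compares two time points and has a direction.

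Section 2.6 (Data analysis and sample size estimation) gives the Phase I stress analysis in one sentence: "Friedman test or linear mixed models will be used to test changes in stress measured weekly from Time 0 to Time 4". It states no rule for choosing between the two methods and names no contrast.

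Section 2.4 (Procedures) confirms five measurement times. Besides the longer surveys at Day 0 and Day 28, "the surveys at Time 1 (Day 7), Time 2 (Day 14), and Time 3 (Day 21) will take about 3 to 5 minutes".

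On size, section 2.6 says "For Phase I, a sample size of 12 is considered" and "To account for a 20% attrition rate, Phase I study will enroll up to 15 caregivers". It states no power or significance level for Phase I.

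**The concern.** The Friedman test ranks each caregiver's five weekly scores and asks whether the mean ranks differ anywhere among the five weeks. A significant result says that some week differs from some other week. It does not say that Day 28 is below Day 0, which is what section 2.1 hypothesises.

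The distinction matters in this setting. The baseline visit falls within seven days of the stem cell infusion (section 2.4), and the Introduction describes complications and heavy support needs during and after treatment. A temporary rise in caregiver stress in the middle weeks is plausible. Friedman could then be significant with no net change by Day 28, and the result could be reported as bearing on the improvement hypothesis.

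There is also a practical cost. The standard Friedman test needs complete blocks, so a caregiver with both Day 0 and Day 28 scores who misses one short weekly survey is lost. With 12 evaluable caregivers planned, each such loss is one twelfth of the sample.

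**Working it through.** **The plan's own figure.** 12 evaluable caregivers with 20% attrition: 12 / (1 − 0.20) = 15, as stated. No Phase I power figure exists to reproduce.

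**Inputs from the protocol.** Five time points and n = 12 are the Phase I figures. The correlation of 0.80 is borrowed from the Phase II calculation ("based on an effect size of 0.6 and correlation of 0.80 between two time points from our previous stress reduction study"), and so is the significance level ("with 80% power and type 1 error of 0.05").

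**Inputs assumed.** Normal scores with SD 1, equal correlation between all pairs of weeks, no missing data, 0.5 as a second correlation value, and the shape and size of the mid-course rise.

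**Test statistics.**
- Friedman: Q = 12 / [n k (k + 1)] × Σ R_j² − 3 n (k + 1), where k = 5 and R_j is the rank sum of week j. Q is referred to chi-square with 4 df.
- Direct comparison: paired t = mean(d) / [SD(d) / √n], with d = Day 28 score − Day 0 score.

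**Why a small rise is enough.** The SD of a within-caregiver difference between two weeks is √[2(1 − r)].
- r = 0.8: √0.4 = 0.632, so a 0.3 SD rise is 0.3 / 0.632 = 0.47 difference-SDs and a 0.6 SD rise is 0.95.
- r = 0.5: √1.0 = 1.0, so the same rises are 0.3 and 0.6 difference-SDs.

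High within-person correlation therefore makes a modest temporary rise easy for an omnibus test to detect.

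**Rejection rates by simulation, n = 12, Day 28 mean equal to Day 0 mean** (two-sided 0.05; rounded, with simulation error of about a point):

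| Mean course, Days 0/7/14/21/28 (SD units) | r | Friedman | Paired t, Day 28 − Day 0 |
|---|---|---|---|
| flat | 0.8 | 5% | 5% |
| 0 / 0.3 / 0.3 / 0 / 0 | 0.8 | 35% | 5% |
| 0 / 0.6 / 0.6 / 0 / 0 | 0.8 | 95% | 5% |
| 0 / 0.3 / 0.3 / 0 / 0 | 0.5 | 16% | 5% |
| 0 / 0.6 / 0.6 / 0 / 0 | 0.5 | 57% | 5% |

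Friedman holds its level under a flat course, so the test itself is valid. It answers a different question.

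**The mixed model.** Read as an overall time effect, it behaves like Friedman: 45% and 98% for the 0.3 and 0.6 SD rises at r = 0.8. Read as the Time 4 minus Time 0 contrast, it estimates the hypothesised quantity and can keep a caregiver who misses an intermediate survey.

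**Power when the hypothesis is true** (n = 12, r = 0.8):
- Steady fall to −0.6 SD at Day 28: Friedman 69%, paired t 85%.
- Drop to −0.6 SD from Day 14, sustained: Friedman 95%, paired t 85%.

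Neither approach is uniformly more powerful, so power does not decide the matter.

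**The case against.** **The contrast may be in a document not shown.** An article often leaves pairwise contrasts to the full protocol or analysis plan. This is fair for the mixed-model branch, which could supply the contrast without contradicting the article. It does not clear the Friedman branch: the article names a test whose null differs from the stated hypothesis, and carrying out that branch as written leaves the hypothesis untested.

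**Rejection after a rise and return is not a false positive for weekly change.** This is correct. Section 2.6 speaks of weekly changes, and in that scenario weekly stress did change. The problem arises only if the p-value is read against the Day 28 hypothesis in section 2.1.

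**The hypothesis can be read as a statement about most participants.** The sentence in section 2.1 opens with the majority of caregivers, so its outcome part could mean the proportion who improve. Friedman does not answer that reading either.

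**Stronger readings that the documents do not support.**
- A reader might infer that neither named method can test Day 28 against Day 0. The mixed model can.
- A reader might infer that Friedman is at fault for being significant under worsening. Any two-sided test shares this: for a linear worsening to +0.6 SD (n = 12, r = 0.8), Friedman rejects in about 68% of trials and the two-sided paired t-test in about 85%. The sign would be visible in the weekly scores.
- A reader might infer a general loss of power. The early sustained drop above reverses it.
- A reader might infer that a misleading stress result could wrongly start Phase II. Section 2.1 ties changes before Phase II to weaknesses such as dissatisfaction or headset discomfort, and no decision rests on a stress p-value.

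**Conclusion.** The point holds in a limited form. One of the two named Phase I analyses does not test the stated Day 28 versus Day 0 hypothesis. Under temporary rises of 0.3 to 0.6 SD with no net change, it would be significant in about 35% to 95% of trials at correlation 0.8 and about 16% to 57% at 0.5, against about 5% for the direct contrast. These rates rest on the assumed size and shape of the rise, normal scores, equal correlations, complete data, and the use of Phase II's 0.80 and 0.05 for Phase I. They show what can happen and do not predict it; a smaller rise gives a lower rate. The structural point, an omnibus null set against a two-point hypothesis, needs none of these assumptions.

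The impact is minor. Phase I assesses feasibility and acceptability, its sample size is not based on a stress test, and effectiveness is tested in Phase II.

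**What to change.** Replace the Phase I stress sentence in section 2.6 with wording such as: *The Phase I stress hypothesis will be assessed by the Time 4 minus Time 0 change in PSS, with its 95% CI, from a linear mixed model with time as a categorical factor; if the model does not converge, a paired t-test or Wilcoxon signed-rank test on the change will be used. The Friedman test or overall time effect will be reported only to describe the weekly course.*

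The model should not force equal correlations across weeks. With correlation that decays over time and no true change, the contrast from an equal-correlation model rejected in about 15% of simulated trials.

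The cost is one sentence, with no new data, participants or visits. There are two downsides. A change confined to the middle weeks would no longer count as support for the hypothesis. Power can also be lower than with the omnibus test if improvement comes early and is sustained (85% against 95% in the example above).

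### The Phase II analysis should name the Day 28 contrast and adjust for baseline PSS; the only adjustment rule stated covers demographic covariates picked by significance

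*Protocol article*

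**What the plan says.** Section 2.1 (Design) hypothesises that "caregiver participants assigned to Active VR will show improved levels of stress and symptoms at Time 4 compared to those assigned to Sham VR". The time point is therefore fixed at Day 28.

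Section 2.6 (Data analysis and sample size estimation) gives the Phase II method in one sentence: "linear mixed repeated measures analysis will be used to analyze the effects of Active VR on stress compared to Sham VR". No visit, group-by-time term or baseline term appears there. The only rule on adjustment follows: "Any demographic covariates will be included in the model if significantly associated with the outcomes and significantly different between the two groups".

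The sample size in the same section is "based on an effect size of 0.6 and correlation of 0.80 between two time points from our previous stress reduction study", "with 80% power and type 1 error of 0.05", for a two-sided test, and concludes that "we will need 39 caregiver participants in each group and a total sample size of 78". Neither the two time points behind 0.80 nor the standard deviation that scales 0.6 is named.

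Section 2.4 (Procedures) has every participant complete a survey at each time point, Time 0 included. I take the PSS of section 2.5.3 to be the stress measure and to be part of that survey.

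**The concern.** The hypothesis is about one visit, but the analysis sentence is not tied to any visit. A repeated-measures model on Times 0 to 4 can yield several group comparisons: an average over visits, a change from Time 0 to Time 4, or the difference at Time 4. They have different expected values and different precision, so the choice should not stay open.

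The adjustment rule is also weak. In a randomised trial baseline differences arise by chance, so a significance test of imbalance is a poor reason to adjust, and it makes the final model depend on the data. The variable most likely to predict Day 28 stress is Time 0 stress. It is not demographic, so the stated rule does not reach it.

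**Working it through.** **Inputs.** Effect 0.6, correlation ρ = 0.80, two-sided 0.05, power 80%, 39 per arm (all section 2.6). Assumptions of mine: equal variances over time, ρ = 0.80 between baseline and Day 28, and 0.6 in raw-SD units unless stated otherwise.

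**Step 1: the plan's own figure.** With V the variance factor relative to one PSS measurement,

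n per arm = 2 × V × (1.960 + 0.842)² / 0.6² = 43.60 × V.

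- V = (1 + ρ)/2 = 0.90 gives 39.24, with 79.8% power at 39 per arm. This matches the stated 39.
- V = 0.85 (mean of four post-baseline visits, compound symmetry) gives 37.06, that is 38 by the normal formula and 39 by the t distribution.
- V = 1 (Day 28 alone, unadjusted) gives 44; V = 2(1 − ρ) = 0.40 (change) gives 18; V = 1 − ρ² = 0.36 (baseline-adjusted) gives 16. None of these matches.

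The factor 0.90 has two readings. It is the variance of an average over two time points. It is also the baseline-adjusted variance when 0.6 is in change-SD units, because (1 − ρ²) / [2(1 − ρ)] = (1 + ρ)/2. The sample size therefore does not settle which contrast was intended.

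**Step 2: three ways to estimate the Day 28 effect.** Power is by noncentral t at 39 per arm.

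| Contrast | V | Power, 0.6 in raw SD |
|---|---|---|
| Day 28 difference, baseline not used | 1.00 | 74.4% |
| Change from Time 0, arm means free | 0.40 | 98.5% |
| Day 28 difference, baseline-adjusted | 0.36 | 99.2% |

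Adjusted against change: 0.36/0.40 = 0.90, a 10% lower variance. The general formula is 1 − (1 + ρ)/2 = (1 − ρ)/2, which gives 25% at ρ = 0.5, 15% at 0.7, 10% at 0.8 and 5% at 0.9. This ratio does not depend on how the 0.6 is scaled. Power does: if 0.6 is in change-SD units, V becomes 1.00 for the change contrast and 0.90 for the adjusted one, and power is 74.4% against 78.7%.

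**Step 3: chance imbalance.** Let d be the observed baseline difference in SD units. The change contrast subtracts all of d, whereas the best prediction of its effect at Day 28 is ρd. The estimate is then off by (1 − ρ)d = 0.2d. By chance d has standard deviation √(2/39) = 0.226, so the typical error is 0.2 × 0.226 = 0.045 SD. This is the same quantity as the variance gap: 0.40 − 0.36 = 0.04 = 0.2².

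**Step 4: a group effect averaged over Times 0 to 4.** Randomisation makes the expected Time 0 difference zero. With a true Day 28 effect of 0.6:

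- full effect from Time 1: average 4 × 0.6 / 5 = 0.48;
- linear build-up: (0 + 0.15 + 0.30 + 0.45 + 0.60)/5 = 0.30.

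Under compound symmetry V = (1 + 4 × 0.80)/5 = 0.84, and power is 62.7% or 29.7%.

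**The case against.** The strongest reply is that a journal article condenses the full protocol, and model terms commonly sit in a document not shown. Several stronger readings do fail on this ground.

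- A reader might infer that only demographic covariates are admitted and that baseline PSS goes unused. The article does not say so. Its rule concerns demographic covariates and is silent on others. A model with Time 0 as a response and a group-by-time contrast would use baseline.
- A reader might infer that the primary test averages over Time 0, and so set 30% or 63% power against 99%. No such contrast is stated. Read with section 2.1, the Day 28 comparison is the more natural intention, and the averaged effect is the least favourable reading.
- A reader might take 0.80 as the plan's baseline-to-Day 28 correlation. That is plausible, but the article does not name the two time points.
- Baseline adjustment may already be inside the 39 per arm, on the change-SD reading of Step 1.

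It is also fair that, in raw-SD units, the gain over an ordinary change contrast is 0.7 percentage points of power (98.5% to 99.2%).

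What stands is narrower. The article does state an analysis sentence and an adjustment rule. The first does not carry through the Time 4 contrast of its own hypothesis. The second is a significance-driven choice that does not provide for the most useful covariate. Both can be improved at no cost.

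**Conclusion.** The point holds as a free improvement to the stated method, not as a proven error. Naming the Day 28 contrast and adjusting for baseline PSS lowers the variance of that contrast by 10% against an unconstrained change contrast, if 0.80 is the baseline-to-Day 28 correlation and variances are equal over time. The range is 5% to 25% for correlations of 0.9 to 0.5. Adjustment also takes out of the estimate the chance-imbalance error of about 0.045 SD that the change contrast leaves in. The power figures depend further on the unstated scale of the 0.6 and should not be read as the plan's actual power. The diluted average over Time 0 is a reading to close off, and nothing in the article shows that it is planned.

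**What to change.** In section 2.6, or in the governing analysis document:

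1. Name the Day 28 Active-minus-Sham difference in PSS as the single primary contrast from the mixed model.
2. Adjust for baseline PSS whatever the observed imbalance. Either model Times 1 to 4 with arm, visit, arm-by-visit, baseline PSS and baseline-by-visit, or keep Time 0 as a response with the arm means constrained equal there. The constraint matters: with free Time 0 means and complete data, the Day 28 difference is the unadjusted one (V = 1.00 in Step 2).
3. Replace the significance screen with demographic covariates chosen in advance, or none.
4. Say which two time points the 0.80 refers to and which SD scales the 0.6, so that the sample size can be matched to the named contrast.

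The cost is analysis wording only. The Time 0 survey is already planned for everyone, and no visit, measure or participant is added.
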